### Baseline Testing (Visit 2)

At least three days after Visit 1 to allow for completion of their food record, participants will return to the lab to complete their first testing session and begin following the resistance training and supplementation regimens. Participants will first have their body mass assessed before providing a urine sample and completing their body water, DEXA assessments (i.e. 4-compartment assessment), and muscle thickness via ultrasound. This scan will be done between the hours of 0600-1000 following an overnight fast and hydration levels will be standardized through the use of urine specific gravity measurements using a hand-held refractometer. Participants will be sent a hydration protocol to follow 24 hours prior to their visit to help ensure adequate hydration levels. This protocol will instruct the participants how much water they should be consuming throughout the day. Prior to testing, participants will complete the same standardized warm-up consisting of 5 minutes of light cycling, 10 body weight squats, 10 body weight walking lunges, 10 dynamic walking hamstring stretches (straight-leg march), and 10 dynamic walking quadriceps stretches. After the warm-up,

participants will complete five CMJ with their hands on their hips. One minute of rest will be observed between each CMJ. Participants will have their maximal voluntary isometric contraction (MVC) completed using an isometric mid-thigh pull. Three attempts will be made and one minute of rest will be observed between each test. Participants will then have their 1RM determined using the leg press exercise. Three minutes of rest will be provided after 1RM is determined and each participant will perform repetitions to failure using 80% of their previously determined 1RM to determine their repetitions to fatigue (RTF). An additional 3-minute break will be observed and then bench press 1RM and RTF will be completed using identical procedures as the leg press exercise. After observing a three-minute rest period after completion of the bench press RTF participants will complete a Wingate using a load that is equivalent to 7.5% of their body mass to measure anaerobic capacity (Lode Excalibur Sport, Lode, Netherlands). Participants will then complete an education session with a research team member to outline the dietary goals they are required to meet throughout this study. This study visit will take approximately 90 minutes to complete.

In a randomized, double-blind, placebo-controlled fashion, participants will be matched according to their Visit 2 fat-free mass to ingest either two grams of dileucine, two grams of leucine, or a placebo (rice flour). All supplements will be provided by Ingenious Ingredients, L.P. (Lewisville, TX). On days where research participants will complete the exercise program, they will be required to consume their daily dose within 60 minutes of completing their workout. When the workout is completed at our facility, supplement ingestion will be monitored by a research team member. On non-training days, participants will consume their assigned dose with their morning meal. Participants will be given enough supplement for one week at a time as participants will be required to schedule and complete one workout per week under the direct supervision of a research team member. During these weekly workouts and check-in visits, participants will get more supplement, discuss their dietary compliance and ensure completion of their workout cards. Participants will continue to follow the prescribed resistance training program for the entire 10 weeks of the study protocol.

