**STATISTICAL ANALYSIS:**

All analyses will be completed using Microsoft Excel and the Statistical Package for the Social Sciences (v23; SPSS Inc., Chicago IL). Before any statistical tests are performed, data will be analyzed for normality, skewness, and kurtosis. All non-normal data will be log-transformed prior to analysis. For all statistical tests, data will be considered statistically significant when the probability of a type I error is 0.05 or less. Primary endpoints for this investigation will be considered to be the delta (Week 10 – Week 2) value for DEXA fat-free mass and leg press 1RM. Secondary endpoints will be delta (Week 10 – Week 2) values for DEXA fat, DEXA lean and DEXA % fat along with bench press 1RM, bench press repetitions to fatigue, leg press repetitions to fatigue, leg press volume, peak anaerobic power, mean anaerobic power, and rate of fatigue. 2 x 2 mixed factorial (group x time) ANOVA with repeated measures on time will be used to determine any statistically significant differences for time and group main effects and group x time interaction effects. Additionally, 95% confidence intervals will be constructed of the observed changes for each group to assess within and between-group changes. All data will be presented as means  $\pm$  standard deviations.

\*required

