| Heart Rate / Blood Pressure                   | X                      | X                                                                                  | X                   | X                   | X                    |
| Food Record*                                  | X                      | X                                                                                  | X                   | X                   | X                    |
| Randomization into Group                      | X                      |                                                                                    |                     |                     |                      |
| Body Composition                              |                        | X                                                                                  | X                   | X                   | X                    |
| One-Repetition Maximum (1RM)                  | X                      | X                                                                                  | X                   | X                   | X                    |
| Isometric Mid-Thigh Pull                      | X                      | X                                                                                  | X                   | X                   | X                    |
| Countermovement Jump                          | X                      | X                                                                                  | X                   | X                   | X                    |
| Muscular Endurance                            |                        | X                                                                                  | X                   | X                   | X                    |
| Anaerobic Capacity                            | X                      | X                                                                                  | X                   | X                   | X                    |
| Dietary Protocol*                             |                        | X                                                                                  | X                   | X                   | X                    |
| Resistance Training Program*                  |                        | X                                                                                  | X                   | X                   | X                    |

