## Procedures

### Body Mass

Body mass weight will be measured (Tanita BWB-627A, Tokyo, Japan) and recorded to the nearest  $\pm 0.1$  kg upon arrival at all study visits. The recorded body mass during visit 1 and visit 2 will be compared to ensure the participant is weight stable and any participant whose body mass changes by more than 3% during this time will be excluded from participation. In addition, body weight will be assessed to compare changes seen after completion of the supplementation and resistance training protocols.

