### Body Composition Assessment

To achieve the highest levels of sensitivity and accuracy, a four-compartment body composition model will be employed according to the methods of Wilson et al. 2013 (Wilson, Fan et al. 2013) and Smith-Ryan et al. 2017 (Smith-Ryan, Mock et al. 2017). Body volume and bone mass will be assessed using a dual-energy x-ray absorptiometry (DEXA) scan (Hologic QDR Discovery A, Waltham, MA) on four separate occasions (visits 2, 3, 4, and 5). In addition, the lean tissue component will be estimated to quantify lean and fat-free body masses for each participant. Participants will be required to observe an overnight fast in order to ensure an accurate determination of body composition and hydration will be standardized using urine specific gravity measurements by a urine refractometer. All DEXA scans will occur during the hours of 0600 and 1000 by graduate assistants or faculty trained in DEXA administration and analysis. Prior to each

day of testing, the device will be calibrated according to manufacturer guidelines. All scans will be completed according to device specifications.

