### ***Supplementation Protocol***

After following the dietary protocol and resistance training program all individuals determined to be weight stable will be randomly assigned to ingest one daily dose in a double-blind fashion of 2 grams of dileucine (Ingenious Ingredients, Lewisville, TX), 2 grams of leucine (NNB Nutrition), or 2 grams of rice flour (placebo). Each dose will be mixed with approximately eight ounces of cold water. On workout days, participants will ingest their assigned dose within 60 minutes of completing their workout. On non-workout days, one dose will be ingested with their morning meal. Participants will be randomly matched according to DEXA fat-free mass for supplementation assignment.

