## What disqualifies a participant for your research?

---

*Please include all exclusion criteria.*

25.

- Female
- Participants who are determined to not be weight stable defined as week 0 and week 2 body mass levels deviating by 3% or more.
- Any individual who is currently being treated for or diagnosed with a cardiac, respiratory, circulatory, musculoskeletal, metabolic, immune, autoimmune, psychiatric, hematological, neurological or endocrinological disorder or disease.
- Body mass index  $> 25 \text{ kg/m}^2$ . Individuals with a body mass index greater than  $25 \text{ kg/m}^2$ , but a body fat percentage less than 25% fat will be accepted into the study
- Individuals who present with any previous injury or illness that would prevent them from appropriately completing all exercise lifts.
- Participants who are not able to fit onto the DEXA table will not be able to participate in the research due to size restrictions of the equipment. This typically includes individuals exceeding 400 pounds or those greater than 6'4".
- Those individuals with less than 12 months of structured resistance training experience will be excluded from the study.
- Individuals whose maximal relative upper body strength is below 1.0 will be excluded.
- Individuals whose maximal relative lower body strength is below 1.5 will be excluded.
- All participants who DO NOT abstain from taking any additional forms of nutritional supplementation deemed to be ergogenic or that will impact resistance training adaptations (pre-workouts, creatine, beta-alanine, etc.) for four weeks prior to beginning this study and for the entire duration of the study.
- Individuals who are currently using or have used within the past 12 months anabolic-androgenic steroids.

\*required

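### Table 1 randomises at Visit 1, before the fat-free mass used for matching exists and before weight stability can be checked; separately, the planned ANOVA leaves out the matching variable

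*Protocol*

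**What the plan says.** **Time of allocation.** The Protocol points to three different times.

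- Baseline Testing (Visit 2): after describing the Week 0 tests, the text says that "participants will be matched according to their Visit 2 fat-free mass" when assigned to dileucine, leucine or placebo.
- Table 1 (printed under Final Study Visit (Visit 5)): the row "Randomization into Group" has a single mark, in the Pre-Study (Visit 1) column. The body composition row starts one column later, at Week 0 (Visit 2).
- Supplementation Protocol: assignment follows the dietary protocol and the training programme and is limited to men already judged weight stable. The section adds: "Participants will be randomly matched according to DEXA fat-free mass for supplementation assignment".

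**First measurement of the matching variable.** Body Composition Assessment schedules DEXA "on four separate occasions (visits 2, 3, 4, and 5). In addition, the lean tissue component". The body water measurements have the same four visits. There is no body composition result at Visit 1.

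**Eligibility checks that bear on the timing.**

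- Body Mass compares Visits 1 and 2: "any participant whose body mass changes by more than 3% during this time will be excluded from participation". Familiarization and Entry (Visit 1) describes the same comparison.
- The exclusion criteria (Question 25) use a different interval: "defined as week 0 and week 2 body mass levels deviating by 3% or more".
- The same list excludes men with a body mass index above 25 kg/m², with an exception for those above it: "but a body fat percentage less than 25% fat will be accepted into the study".

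**Analysis.** The Statistical Analysis section (Question 17) states: "2 x 2 mixed factorial (group x time) ANOVA with repeated measures on time will be used". It names no covariate and no blocking or matching factor. The primary changes are Week 10 minus Week 2.

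**The concern.** An allocation made at Visit 1 cannot be matched on a value first obtained at Visit 2. Staff working from Table 1 would do something different from staff working from the narrative. At Visit 1 the strength criterion is known, but weight stability and the body-fat exception are not. A trial of 36 men, 12 per arm, has little room for men who are allocated and then found ineligible.

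The analysis point is separate. Matching on a prognostic variable makes the arms more alike and so reduces the true variability of the difference between them. A model that omits the variable leaves that variation in its error term. Its standard error is then too large, and the precision that the matching was meant to buy is not used.

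**Working it through.** **1. Timing, from the text alone**

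| Item | Earliest time it is known |
|---|---|
| Randomisation mark in Table 1 | Visit 1 |
| Fat-free mass used for matching | Visit 2 |
| Body-fat percentage for the BMI exception | Visit 2 |
| Weight stability, Body Mass section | Visit 2 |
| Weight stability, Question 25 | Week 2 (Visit 3) |

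The Table 1 mark comes before every other entry. Moving it to Visit 2 would resolve the first three conflicts but not the last: under the Question 25 wording, weight stability is still unknown at Visit 2.

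The Supplementation Protocol wording is not isolated. An assignment after some training would fit the week 0 to week 2 weight check, the eight weeks of supplementation in the Specific Aims, and the changes taken from Week 2. Experimental Design and Baseline Testing (Visit 2) instead describe ten weeks of supplementation starting from Visit 2. The document does not settle which applies.

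**2. Effect of omitting the matching variable**

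The stated 36 equals 3 × 12. The Protocol gives no power calculation to reproduce and no correlations, so r (matching fat-free mass with the change score) is an assumption shown over a range. With two time points, the group by time interaction is the same test as a one-way comparison of change scores, so the change score is used below.

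With close matching, the unadjusted standard error is too large by the factor 1/√(1 − r²):

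- r = 0.3: 1/√0.91 = 1.048
- r = 0.4: 1/√0.84 = 1.091
- r = 0.5: 1/√0.75 = 1.155

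A simulation ranked 36 men on fat-free mass into 12 triplets, randomised 1:1:1 within each triplet, and applied the three-group F test at nominal 0.05 (6,000 runs per cell). Power is for one arm shifted by 1 SD of the change score.

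| r | Type I error, unadjusted | Type I error, adjusted | Power, unadjusted | Power, adjusted |
|---|---|---|---|---|
| 0 | 0.045 | 0.045 | 0.67 | 0.67 |
| 0.3 | 0.040 | 0.050 | 0.68 | 0.72 |
| 0.5 | 0.018 | 0.048 | 0.66 | 0.80 |
| 0.7 | 0.005 | 0.052 | 0.66 | 0.94 |

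The simulation standard error at 0.05 is √(0.05 × 0.95/6000) = 0.003, so 0.045 at r = 0 is compatible with the nominal level.

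**3. Adjusting for the endpoint's own pre-dose value**

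If the change is taken from the same value that serves as covariate, and variances are equal, adjustment leaves (1 + ρ)/2 of the change-score variance: 0.85 at ρ = 0.7 and 0.95 at ρ = 0.9.

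The stated change is Week 10 minus Week 2, so this ratio does not carry over to a Week 0 covariate. With unit variances, the proportion of variance removed is

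[corr(0,10) − corr(0,2)]² / {2[1 − corr(2,10)]}.

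- Equal correlations: the numerator is (ρ − ρ)² = 0, so nothing is gained.
- First-order autoregressive decay, with ρ the Week 0 to Week 10 correlation: corr(0,2) = ρ^0.2 and corr(2,10) = ρ^0.8.
  - ρ = 0.9: (0.979 − 0.9)² / [2(1 − 0.919)] = 0.0063/0.1617 = 0.039.
  - ρ = 0.5: (0.871 − 0.5)² / [2(1 − 0.574)] = 0.1373/0.8513 = 0.161.

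The reduction therefore runs from zero to about 4–16%.

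For fat-free mass, the Visit 2 value is both the matching variable and the Week 0 value, so steps 2 and 3 describe one loss. Under the decay model the implied r is √0.039 = 0.20 to √0.161 = 0.40 in absolute size, and the standard error is 2 to 9% too large.

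**The case against.** The best defence on timing is that Table 1 contains one misplaced mark. Two narrative sections tie assignment to fat-free mass, and one of them also requires weight stability first, so neither permits allocation at Visit 1. A reader might infer from Table 1 that ineligible men will be randomised and then dropped. The documents do not support that as a prediction: it follows only if staff obey one table cell against explicit text. What stands is that the document contradicts itself, and that correcting the cell alone would leave the two weight-stability definitions and the Supplementation Protocol wording in conflict.

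On the model, covariates are often left to a statistical analysis plan, which is not shown here, and a group by time ANOVA is a valid test. The time levels are not named either, so Week 0 could enter as a repeated measure, though still not as a covariate. This makes the model point secondary. It remains worth raising because the Protocol fixes a specific model beside a specific matching scheme and does not connect them.

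Three stronger readings of the model point fail:

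- That omitting the covariate biases the comparison or inflates false positives. The calculations show a conservative test.
- That baseline adjustment would bring the full (1 + ρ)/2 gain. The stated change starts at Week 2, so a Week 0 covariate does not deliver it.
- That the matching loss and the baseline loss add up for fat-free mass. They are one loss, and matching already limits chance imbalance on that variable.

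**Conclusion.** The timing contradiction is certain and rests on no assumption: allocation at Visit 1 cannot be matched on a Visit 2 value. Its full extent is wider than the table cell, because the weight check and the position of assignment relative to the training programme also conflict between sections.

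The model point holds as a matter of efficiency. Its size depends on correlations that the Protocol does not give. The loss is negligible at r near 0; at r = 0.3 to 0.5 the unadjusted standard error is about 5–15% too large and the actual type I error is about 0.04 to 0.02. A Week 0 value of the same endpoint reduces the variance of the stated change by nothing under equal correlations and by about 4–16% under decaying ones.

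**What to change.** **Timing.** Reconcile Table 1, Baseline Testing (Visit 2), Supplementation Protocol, Body Mass and Question 25 so that allocation has one stated time. It should fall after the DEXA used for matching and after every check that is meant to precede allocation, and before the first dose. Use one definition of weight stability throughout; which one, and when supplementation begins, is for the investigator to settle. Until then, an instruction to allocate at Visit 2 after all eligibility checks cannot be carried out under the Question 25 wording.

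**Model.** Add the matching fat-free mass value and each endpoint's own pre-dose value as covariates. For fat-free mass this is one covariate, provided the matching scan is also the pre-dose value. Decide at the same time which visit the change is measured from, because that determines what the baseline covariate can contribute.

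**Cost.** Edits to one table cell and a few sentences, with no new measurements. Residual degrees of freedom go from 36 − 3 = 33 to 32 or 31, and the two-sided 5% critical t from 2.035 to at most 2.040.

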#### Resistance Training & Supplementation Phase (Visits 3 and 4)

After completing two weeks of resistance training (8 total workouts), participants will return to the lab at a similar time (0600 – 1000 hours) for completion of an identical bout of testing. Prior to this visit, participants will complete another three-day food record and discuss with research team members about their compliance to the diet program. Participants will also have their body mass recorded. Participants will then donate a urine sample to assess hydration before completing a body water, DEXA, and ultrasound assessment. Using identical procedures as before, participants will have their CMJ performance, maximal strength (1RM and isometric mid-thigh pull) and endurance (maximal repetitions at 80% 1RM [RTF]) assessed before completing a Wingate anaerobic capacity test (WanT). New 1RM values will be used to re-assign loads during the following resistance training period. This visit will take approximately 90 minutes to complete.

#### Final Study Visit (Visit 5)

Approximately ten weeks after beginning the resistance training (40 workouts; a minimum of 36 required or 90% compliance) and supplementation protocol, study participants will report back to the lab for their final study visit during a similar time of day (0600 – 1000 hours). In an identical fashion as previously completed, participants will observe an overnight fast, ensure completion of all food and training records, return any remaining supplements and have their body mass, hydration, body water, body composition (DEXA), ultrasound, countermovement jump, maximal strength (bench

press 1RM, leg press 1RM, and isometric mid-thigh pull), muscular endurance (repetitions to failure using 80% [RTF] of their Visit 2 1RM for both exercises) and anaerobic capacity (WanT) determined. This visit is estimated to take 90 minutes to complete.

**Table 1:** Outline of testing for the 10-week study.

| Procedure                                     | Pre-Study
(Visit 1) | Week 0
(Visit 2)                                                                | Week 2
(Visit 3) | Week 6
(Visit 4) | Week 10
(Visit 5) |
|-----------------------------------------------|------------------------|------------------------------------------------------------------------------------|---------------------|---------------------|----------------------|
| Resistance Training Protocol                  |                        | [figure not shown] |                     |                     |                      |
| Supplementation Protocol                      |                        | [figure not shown] |                     |                     |                      |
| Review & Sign Consent                         | X                      |                                                                                    |                     |                     |                      |
| Screening (Health, Medical, Exercise History) | X                      |                                                                                    |                     |                     |                      |
| Height and Weight                             | X                      | X                                                                                  | X                   | X                   | X                    |
| Heart Rate / Blood Pressure                   | X                      | X                                                                                  | X                   | X                   | X                    |
| Food Record*                                  | X                      | X                                                                                  | X                   | X                   | X                    |
| Randomization into Group                      | X                      |                                                                                    |                     |                     |                      |
| Body Composition                              |                        | X                                                                                  | X                   | X                   | X                    |
| One-Repetition Maximum (1RM)                  | X                      | X                                                                                  | X                   | X                   | X                    |
| Isometric Mid-Thigh Pull                      | X                      | X                                                                                  | X                   | X                   | X                    |
| Countermovement Jump                          | X                      | X                                                                                  | X                   | X                   | X                    |
| Muscular Endurance                            |                        | X                                                                                  | X                   | X                   | X                    |
| Anaerobic Capacity                            | X                      | X                                                                                  | X                   | X                   | X                    |
| Dietary Protocol*                             |                        | X                                                                                  | X                   | X                   | X                    |
| Resistance Training Program*                  |                        | X                                                                                  | X                   | X                   | X                    |
| Exercise Training Compliance*                 |                        | X                                                                                  | X                   | X                   | X                    |
| Review Supplementation Protocol*              | X                      | X                                                                                  | X                   | X                   | X                    |

\* = Will occur weekly online and during in-laboratory study visits

